**FIGURE 1 F1:**
[figure not shown]
The integrated process evaluation framework (IPEF). Adapted from Nielsen et al. (2023, p. 17) and De Angelis et al. (2020, p. 13). *Focus group discussions. **Open-ended surveys.

Employees feel more empowered when they see their managers engage in mutual learning. Such managerial participation may also contribute to stronger relationships among employees and between employees and their managers. Based on this, the researcher will encourage and motivate managers to include and involve their departmental employees in the intervention study, thereby strengthening working relationships and promoting personal empowerment. The researcher will hold departmental meetings with managers and employees to ensure that the intervention study is communicated equally to all prospective participants. Managers will also attend separate meetings and be informed of the potential advantages and challenges associated with intervention studies within organizations to help empower them to motivate and support their employees in participating in the study.

When recruiting participants for the intervention study, encouraging engagement can be challenging, particularly when participants come from diverse cultural and socio-economic backgrounds (Olem et al., 2009), such as those in South Africa (Olem et al., 2009). Non-adherence to intervention activities can undermine the study’s internal validity, skew results, and make interpretation difficult or inaccurate. Such outcomes can ultimately increase the likelihood of the intervention study being regarded as ineffective.

Recognizing the challenges of sustaining participant engagement in intervention studies (Olem et al., 2009) – especially in diverse contexts such as South Africa – the researcher will proactively encourage participation. Specifically, the researcher will emphasize that participation is voluntary and confidential, and clearly distinct from organizational mandates. Potential doubts or hesitations participants may experience will be openly addressed and normalized. During training and orientation, participants will be invited to identify potential barriers to their engagement, enabling the researcher to collaboratively problem-solve these issues (see Tables 1, 2 for details). Participants will also receive the researcher’s direct contact information, ensuring accessible support and assistance. The researcher will emphasize respect and appreciation for each participant’s contribution and clearly communicate how individual involvement will benefit overall study outcomes and personal development. Regular contact and reminders will reinforce participants’ sense of inclusion and engagement throughout the study, enhancing ongoing commitment (Buchanan and Hvizdak, 2009).

The researcher will also do check-ins with participants to maintain awareness of the study. Research has shown that participants are more likely to engage with research if they are reminded (Buchanan and Hvizdak, 2009). All personal information will only be used for research purposes, accessible only to the research team, and will be destroyed after feedback. The research study has ethics clearance from the North-West University’s Economics and Management Sciences Research Ethics Committee (NWU-01874-22-A4).

### Sample size and power

2.4

It is important to determine the optimal sample size to enable effective statistical analysis. Accordingly, an *a priori* power analysis using G*Power indicated that at least 26 participants per group would be required for a large effect (Cohen’s *d* = 0.80) and 51 for a medium effect (Cohen’s *d* = 0.50). These estimates were based on an alpha level of 0.05 and 80% power (Faul et al., 2007).

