#### Effect evaluation data analysis plan

2.8.2

Background characteristics will be presented by means of descriptive statistics. Demographic characteristics (i.e., participants’ educational level, age, gender, ethnicity, organization and job tenure, duration reporting to manager, and department) will be used to determine the representativeness of the study sample and potentially to control for their impact on the effects (Bernerth and Aguinis, 2016).

We articulated the following directional hypotheses (H1 to H3) to evaluate the effectiveness of the intervention:

Hypothesis 1a (within-group): both Group 1 (dual-level) and Group 2 (employee-only) will show significant increases in need crafting behaviors from baseline to the 2-weeks and 1-month post-intervention follow-ups.

Hypothesis 1b (between-group): Group 1 will show significantly greater increases in need crafting behaviors compared to Group 2 at the 2-weeks and 1-month follow-ups.

Hypothesis 1c (sustainability): Group 1 will maintain higher levels of need crafting from the 2-weeks to the 1-month follow-up, while Group 2 may show some decline.

Hypothesis 2a (within-group): Group 1 will show significant increases in perceived need-supportive leadership behaviors from baseline to the 2-weeks and 1-month follow-ups, while Group 2 will show minimal or no change.

Hypothesis 2b (between-group): Group 1 will show significantly higher perceived need-supportive leadership behaviors compared to Group 2 at the 2-weeks and 1-month follow-ups.

Hypothesis 2c (sustainability): Group 1 will maintain elevated levels of perceived need-supportive leadership from the 2-weeks to the 1-month follow-up, while Group 2 will remain stable at baseline levels.

Hypothesis 3a (within-group): both groups will show increases in need satisfaction from baseline to the 2-weeks and 1-month follow-ups.

Hypothesis 3b (between-group): Group 1 will show significantly greater improvements in need satisfaction compared to Group 2 at the 2-weeks and 1-month follow-ups.

Hypothesis 3c (sustainability): Group 1 will maintain or further improve need satisfaction from the 2-weeks to the 1-month follow-up, while Group 2 effects may diminish over time.

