Based on theoretical proximity to training content and previous research, the largest between-group differences were expected for perceived need-supportive leadership (the direct target of the leader intervention), followed by need satisfaction (downstream of both crafting and leader support), with more modest effects anticipated for need crafting behaviors (since both groups directly received crafting training).

In the intervention study, linear mixed-effects models (LMMs) will be used to evaluate the effects of interventions on need crafting behaviors, need satisfaction, and need-supportive leader behaviors (i.e., to test these hypotheses). LMMs are ideal for this design because they handle repeated measures (pre-test, post-test, and follow-up) and account for the nesting of participants within departments, addressing both individual and group-level variability. By modeling random effects for participants and departments, LMMs ensure that differences in responses over time and between groups are properly accounted for. Additionally, LMMs effectively manage missing data, allowing us to test interaction effects between time and group and providing a robust evaluation of intervention outcomes across multiple levels (e.g., Snijders and Bosker, 2012).

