### Limitations

3.1

Several limitations of the proposed protocol should be emphasized. First, the design is quasi-experimental: although departments will be randomized to the immediate (Group 1) and delayed (Group 3) conditions, Group 2 will comprise departments whose managers do not volunteer and are therefore self-selected. Pre-existing differences between Group 2 and the randomized groups (e.g., in leadership quality or departmental climate) may confound between-group comparisons, as manager willingness to participate may in itself signal a more need-supportive environment. Second, the study will be conducted at a single site of one South African mining services organization and is restricted to white-collar employees, which constrains the generalizability of findings to blue-collar workers – for whom safety protocols structurally limit crafting opportunities – and to other industries, labor markets, and cultural contexts. Third, although the *a priori* power analysis indicates that 26–51 participants per group are required to detect large-to-medium effects, this calculation assumes independent observations; because participants are clustered within departments, non-trivial intraclass correlations will reduce the effective sample size and statistical power, and attrition across the six measurement waves may compound this. Because the planned linear mixed-effects models include department-level random effects, clustering is accounted for analytically rather than biasing estimates; the residual concern is statistical power, and the study may only be adequately powered to detect moderate-to-large effects. Fourth, because all groups will be drawn from a single organization, contamination is possible: employees and managers from different conditions interact daily and may share intervention content, diluting between-group differences.

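### The sample sizes of 26 (d = 0.80) and 51 (d = 0.50) per group cannot come from one t-test specification: two-sided gives 26 and 64, one-sided gives 21 and 51

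*Protocol article*

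**What the plan says.** Section 2.4 (Sample size and power) says that an a priori G*Power analysis "indicated that at least 26 participants per group would be required for a large effect", defined as Cohen's d = 0.80, "and 51 for a medium effect", defined as d = 0.50. It adds: "These estimates were based on an alpha level of 0.05 and 80% power". It does not name the test or say whether it is one-sided or two-sided.

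Section 2.8.2 labels hypotheses H1 to H3 as directional, but does not say that the tests will be one-sided. The planned analysis is a linear mixed model with random effects for participants and departments.

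Section 2.5 treats each department that signs up as a cluster and randomizes departments to Group 1 or Group 3.

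Section 3.1 (Limitations) repeats that the "power analysis indicates that 26–51 participants per group are required to detect large-to-medium effects". It concedes that this calculation takes observations as independent and that intraclass correlation and attrition will lower power. It then says that "the study may only be adequately powered to detect moderate-to-large effects". It gives no ICC, department size or recalculated figure.

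**The concern.** The two figures are presented as the output of one analysis at one alpha and one power. Required sample size scales closely with 1/d², so going from d = 0.80 to d = 0.50 should multiply it by about (0.80/0.50)² = 2.56. The printed ratio is 51/26 = 1.96. Either the two numbers rest on different tests, or one of them is wrong.

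At stake is the meaning of the medium-effect figure. A reader who takes 26 as the guide to the specification will assume two-sided testing, and will then believe that 51 per group gives 80% power at d = 0.50 when it does not. The Limitations section carries the same range forward as the starting point for its statement on power. The article also offers itself as a standardized protocol, so others may reuse the pair.

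**Working it through.** **Inputs.** From section 2.4: d = 0.80 and 0.50, alpha 0.05, power 80%, n per group (so equal groups). Sidedness is not stated, so both are tried. ICC and department size are not given anywhere, so the values used in step 4 are assumptions.

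**Step 1: reproduce the printed figures.** Two-sample t test, exact noncentral t, df = 2n − 2, noncentrality d·√(n/2); smallest n with power of at least 80%:

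| | d = 0.80 | d = 0.50 |
|---|---|---|
| Two-sided | **26** (80.7%; 25 gives 79.1%) | 64 (80.1%; 63 gives 79.5%) |
| One-sided | 21 (81.7%; 20 gives 79.9%) | **51** (80.6%; 50 gives 79.9%) |

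Each printed number is matched to the unit, but 26 only by the two-sided test and 51 only by the one-sided test.

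**Step 2: look for another single test that gives both.** A paired t test gives 15 and 34 (two-sided) or 12 and 27 (one-sided). A two-group ANOVA gives 26 and 64. A three-group ANOVA gives 22 and 53. None gives 26 and 51 together.

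**Step 3: power at the printed sizes.**

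- 51 per group at d = 0.50: 80.6% one-sided, 70.6% two-sided. The two-sided requirement of 64 is 64/51 = 1.25 times the printed figure.
- 26 per group at d = 0.80: 80.7% two-sided, 88.5% one-sided.

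**Step 4: what clustering does, under stated assumptions.** Design effect DE = 1 + (m − 1)·ICC, effective n = n/DE, detectable d ≈ (z for alpha + 0.842)·√(2/effective n), with z = 1.960 two-sided or 1.645 one-sided. For n = 51 and m = 10 per department (assumed):

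| ICC (assumed) | DE | Effective n | Detectable d, two-sided | Detectable d, one-sided | Power at d = 0.50, two-sided / one-sided |
|---|---|---|---|---|---|
| 0.05 | 1 + 9 × 0.05 = 1.45 | 35.2 | 2.802 × √(2/35.2) = 0.67 | 2.487 × √(2/35.2) = 0.59 | 54% / 67% |
| 0.10 | 1 + 9 × 0.10 = 1.90 | 26.8 | 2.802 × √(2/26.8) = 0.76 | 2.487 × √(2/26.8) = 0.68 | 44% / 56% |

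These use individual-level degrees of freedom. Counting degrees of freedom by department would lower power further.

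**Step 5: possible offset from baseline adjustment.** At an assumed baseline correlation of 0.5 the variance factor is 1 − 0.5² = 0.75, so detectable d shrinks by √0.75 = 0.866. The one-sided values become 0.51 to 0.59 and the two-sided values 0.58 to 0.66. At ICC 0.03 (DE = 1.27) the one-sided value is 0.48. The article claims no such gain.

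**The case against.** **The error may be harmless.** The hypotheses are called directional. If all tests are one-sided, 51 is right and 26 exceeds the 21 that is needed. This stands: the shortfall at 51 per group, before clustering, depends on two-sided testing. It does not rescue the pair, because one of the two numbers then still fails to match its stated 80%.

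**A reader might infer that neither figure delivers 80% power once departments are allocated.** The article does not support that without conditions. One-sided, 26 per group at d = 0.80 still has 80.8% power at ICC 0.03 with departments of 10 (individual-level degrees of freedom). The answer turns on tails, ICC and department size, none of which is given.

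**Clustering is already disclosed.** Section 3.1 says that the figures assume independence and that power will suffer. A reader might infer that its closing remark on moderate-to-large effects is false. It is hedged, and on the article's own labels (0.50 medium, 0.80 large) a detectable d of 0.67 to 0.76 falls inside that range. The remark is imprecise rather than wrong.

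**A reader might also infer that the need-crafting contrast is hopelessly underpowered**, because section 2.8.2 speaks of effects "with more modest effects anticipated for need crafting behaviors". That phrase ranks need crafting below the other two outcomes and gives no effect size, so no power figure follows from it. Nor does the article set any rule for reading a null result as no benefit.

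**Conclusion.** The pair 26/51 is wrong as written. No single equal-group two-sample t test at alpha 0.05 and 80% power yields both, and this needs no assumption about ICC or department size. Which number is at fault depends on a sidedness that the article does not state: two-sided, the medium-effect figure should be 64, and 51 gives 70.6% power; one-sided, the large-effect figure should be 21, and 26 is on the safe side.

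The clustering element is an admitted weakness that has not been quantified. With 10 per department and ICC 0.05 to 0.10, both assumed, 51 per group does not give 80% power at d = 0.50 on either tail before baseline adjustment. It should not be stretched to say that both printed figures fail in every case or that the power statement in Limitations is untrue.

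**What to change.** 1. In section 2.4, name the test and one sidedness for both figures, and print the matching pair: 26 and 64 if two-sided, 21 and 51 if one-sided.
2. In section 3.1, change the range to match (26 to 64, or 21 to 51).
3. State that these are unclustered minimums, and give the detectable effect at the planned group size for a stated range of department size and ICC, using 1 + (m − 1) × ICC. If a gain from baseline adjustment is counted, state the assumed correlation.
4. Put that figure beside the general remark on moderate-to-large effects in section 3.1.

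The cost is wording. The correction itself calls for no extra recruitment and no change of design; the detectable effect on the page becomes somewhat less favourable.

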### Allocation to intervention

2.5

All departments that sign up will be treated as separate clusters, followed by randomization (e.g., using a random number generator) to assign each department to either Group 1 (immediate intervention) or Group 3 (delayed intervention). Participants without participating managers will automatically be assigned to Group 2.

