### Study design

2.1

The current intervention protocol recommends a quasi-experimental mixed-methods design using a partially randomized delayed-start approach with three experimental groups. Departments (clusters) will be randomized to Group 1 (NC + NN) or Group 3 (delayed NC + NN); departments whose managers do not volunteer will form Group 2 (NC only, non-randomized). Group 2 will demonstrate the superiority of a multilevel intervention (i.e., its cumulative effects), whereas Group 3 will serve as a control group until its members have received the intervention.

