The current study will rely on criterion (purposive) sampling, in which participants from selected organizational departments and/or their direct line managers will be included based on specific, predetermined inclusion criteria relevant to the study. For South Africans to be considered employed, they should be “between the ages of 15 and 64” (Statistics South Africa [Stats SA], 2022, p. 2). However, for ethical reasons, participants should be at least 18 and hold at least a Grade 12 certificate to optimally grasp the content of the need-crafting intervention training. The researchers also considered it appropriate that participants had been employed in their position for at least 1 month. Meta-analytic results show a negative association between tenure and job crafting (Rudolph et al., 2017), which may be ascribed to the fixed mental schemas of employees with longer tenure and the resultant impact on behavior (Zacher and Kooij, 2017). At the same time, experience may put them in a better position to craft, as they will know “what” and “how” to craft (Rudolph et al., 2017). Finally, only white-collar employees will be included in the intervention because of the inherent safety risks associated with crafting, for example, among machine operators in the mining sector. The daily operational duties of machine operators generally allow for limited crafting in light of mining safety protocols.

The individual, group, leader, and organizational (IGLO) model proposed by Nielsen et al. (2017) suggests that interventions target the individual, group, leader, and organizational levels. The IGLO model states that an individual-level intervention will have a negligible impact if it does not also address another organizational level (e.g., leaders). Nielsen et al. (2023) suggest that individual-level interventions should focus on enhancing and upholding an employee’s well-being through activity engagement, building personal resources, developing resilience, and ensuring positive coping mechanisms. Given managers’ ability to support their subordinates’ needs (see Slemp et al., 2021 for an overview), the individual-level intervention will be complemented by a leader-level intervention. At the time of NC, the NN intervention (see Tables 1, 2) will offer parallel training to managers, equipping them to support their employees’ basic psychological needs.

**TABLE 1 T1:** Overview of ‘NeedCraft.’

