### Data collection and timeline

2.7

As depicted in Figure 2, all three groups will undergo the same pre-testing simultaneously (before any intervention training commences), and it will comprise the following stages: allocate departments to three groups; perform the pre-test data collection on all three groups at the same time and under the same conditions (T1); provide the first two experimental groups with the intervention supplemented by process and outcome measurements (T2); and provide the delayed experimental group with another baseline measurement of the same pre-test assessment battery to account for any possible changes that may have occurred in the time after they were part of the initial pre-test data collection (T3), as well as commence with post-testing on the first two groups (T3). Thereafter, the third group will receive the intervention (T4), followed by post-testing on all three groups 2 weeks after the training and 1 month after they have completed their intervention training to determine the potential impact on the dependent variable (need satisfaction) within each group as well as measure the possible differences between the groups due to delayed intervention delivery. Each group will undergo two separate post-tests, with all post-testing occurring at four different time points (Demerouti et al., 2021; Laporte et al., 2021).

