Given ethical considerations around withholding intervention opportunities, a delayed experimental group replaces a traditional control group (Putter et al., 2024). We acknowledge potential challenges associated with delayed access, such as reduced motivation and higher dropout (Laporte et al., 2021). Additionally, with increased assurance of participant anonymity, the study seeks to minimize social desirability bias; however, complete avoidance is unlikely in social-science research where subjective interpretations of contexts occur from a personal perspective (Podsakoff et al., 2024).

Considering managers’ significant role in employee well-being – and common managerial uncertainty around providing well-being support – this intervention also deliberately aims to equip managers with practical skills to facilitate employees’ need crafting. If effective, the program can equip organizations with structured tools to proactively enhance employee engagement, well-being, and retention, treating these as downstream outcomes of improved need-supportive design and leadership (Baard et al., 2004; Gagné and Deci, 2005; Slemp et al., 2021). From a theoretical standpoint, the research may refine and extend SDT by demonstrating the complementary roles of managerial support (NN) and employee-driven need crafting (NC), consistent with SDT’s multilevel view of how social contexts shape internalization and high-quality motivation (Ryan and Deci, 2017; Vansteenkiste et al., 2020).

Ultimately, this protocol seeks to bridge theoretical frameworks with real-world application, providing an initial yet systematic exploration of the organizational conditions that enable effective need-crafting and need-support interventions. By documenting mechanisms and context conditions in a non-WEIRD workplace, and by specifying SDT-consistent pathways to be tested in subsequent analyses, the study contributes to an inclusive, practically useful evidence base for Positive Psychological Interventions at work (Duan et al., 2022; Nielsen and Miraglia, 2016).

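### Group 2 is defined by whole departments in most of the protocol but by individual participants in the allocation section; the two rules differ wherever only some of a department's line managers take part

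*Protocol article*

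**What the plan says.** Section 2.1 (Study design) defines the third arm by department: "departments whose managers do not volunteer will form Group 2 (NC only, non-randomized". Section 3.1 (Limitations) repeats this: "Group 2 will comprise departments whose managers do not volunteer and are therefore self-selected". The methods paragraph of the abstract and section 2.7 (Data collection and timeline) also speak of departments being allocated to all three groups.

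Section 2.5 (Allocation to intervention) states the operative rule in two steps. First: "All departments that sign up will be treated as separate clusters, followed by randomization", to Group 1 or Group 3, with no exception for a department whose manager declines. Second: "Participants without participating managers will automatically be assigned to Group 2". The unit has changed from the department to the person.

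Timing matters here. Section 2.7 says the study will "provide the first two experimental groups with the intervention supplemented by process and outcome measurements (T2"), so Group 2 is trained with Group 1, and Group 3 is trained only at T4. Section 2.1 says that "Group 3 will serve as a control group until its members have received the intervention".

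On managers, section 2.2 (Setting and participants) says that "participants from selected organizational departments and/or their direct line managers will be included". No section gives the number of direct line managers per department. Section 2.3 links managers to employees through a department number only.

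**The concern.** Group membership is the exposure in every planned model, so the rule that sets it should give one answer for each employee. Here it gives two whenever a department has several direct line managers and only some of them take part.

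Under the participant rule, employees leave a randomized department because of what their manager chose to do. If that department was randomized to Group 3, the departing employees are trained at T2, inside a department that should still be untreated. Group would also vary within a department, although the department is both the unit of randomization (2.5) and a random effect in the models (2.8.2).

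Under the department rule nobody moves, but some employees counted as NC + NN report on a supervisor who never attended NN. The leader-support scale asks each employee about their own supervisor (2.8.1), and section 2.8.2 expects its largest between-group difference on this outcome. The contrast in Hypothesis 2b would be diluted.

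Allocation comes before the T1 pre-test, so the ambiguity cannot be repaired after the study has started.

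**Working it through.** **Step 1. Compare the definitions.**

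| Place | Unit that enters Group 2 |
|---|---|
| Abstract, methods paragraph | department |
| 2.1 Study design | department |
| 2.7 Data collection and timeline | department |
| 3.1 Limitations | department |
| 2.5 Allocation to intervention | individual participant |

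**Step 2. Apply both rules to the cases that the text allows.**

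| Case | Department rule | Participant rule |
|---|---|---|
| One manager, takes part | department randomized | same |
| One manager, declines before randomization | whole department in Group 2 | all its employees in Group 2: same result |
| Two line managers, one declines; department drawn to Group 1 | if the department counts as volunteering, all are NC + NN, some with an untrained supervisor | employees of the declining manager go to Group 2 |
| Two line managers, one declines; department drawn to Group 3 | if the department counts as volunteering, all wait until T4, and some have a supervisor who will not attend NN | employees of the declining manager receive NC at T2; their colleagues wait until T4 |

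The rules separate only in the last two rows. Section 2.2 refers to direct line managers and does not limit a department to one. Section 2.3 assigns one number per department, which fits one manager or several.

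**Step 3. Illustrate the size.** The article gives no share of affected employees, so 10%, 20% and 30% are assumptions. The effect d = 0.80 with 26 per group is the large-effect benchmark in section 2.4, not a forecast for this outcome. A two-sided two-sample t-test at alpha 0.05 reproduces that 26, with power 80.7%. Clustering is ignored, as in section 2.4.

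*Department rule.* Let p be the share of Group 1 employees whose supervisor is untrained, and assume no NN effect on them. The leader-support difference from Group 2 becomes d(1 − p).

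*Participant rule, analysed as randomized.* Let q be the share moved, equal in both arms and unrelated to outcome. Let NC + NN give d and NC alone give a fraction f of d.
- Group 1 mean shift: (1 − q)d + qfd
- Group 3 mean shift during its control period: qfd
- Difference: (1 − q)d, whatever the value of f

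Both formulas therefore give the same numbers: 0.80 × 0.9 = 0.72, 0.80 × 0.8 = 0.64, 0.80 × 0.7 = 0.56.

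*Participant rule, moved employees dropped from the randomized contrast.* The number per group becomes 26(1 − q): 26 × 0.9 = 23.4, 26 × 0.8 = 20.8, 26 × 0.7 = 18.2.

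| Share | Diluted effect, n = 26 | Power | Remaining n per group, d = 0.80 | Power |
|---|---|---|---|---|
| 0% | 0.80 | 80.7% | 26 | 80.7% |
| 10% | 0.72 | 72.1% | 23.4 | 76.3% |
| 20% | 0.64 | 61.9% | 20.8 | 71.1% |
| 30% | 0.56 | 50.8% | 18.2 | 65.0% |

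Selection bias from unequal movement between arms is not included.

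**The case against.** The best reply is that the participant reading rests on one noun. Four other places allocate departments, so section 2.5 may be shorthand for employees of departments whose manager does not take part. With one manager per department and participation settled beforehand, nobody is misplaced. That is a fair reading and it limits the severity. It does not remove the conflict: section 2.5 is the section that governs allocation, it randomizes every department that signs up without exception, and neither condition is stated.

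A second reply is that section 3.1 already discloses self-selection into Group 2 and contamination between conditions. It does, but it treats Group 2 as whole departments. It does not consider two conditions created inside one department by the allocation rule.

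A third reply is that Hypotheses 1 to 3 are worded around Groups 1 and 2, so no numbered hypothesis tests Group 1 against Group 3. This is correct. The harm under the participant rule falls on the protocol's only randomized contrast, not on a numbered hypothesis. The dilution under the department rule does reach Hypothesis 2b.

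A reader might also infer that employees change group whenever a manager withdraws after randomization, and more often in the delayed arm. The documents do not support this. The sentence in section 2.5 describes a one-time assignment, and section 2.7 places allocation before the pre-test. The Discussion says only: "We acknowledge potential challenges associated with delayed access, such as reduced motivation and higher dropout". That is a possible challenge, not an expectation, and managers are not mentioned.

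**Conclusion.** The inconsistency is real and lies in the allocation rule. It has consequences only if some department has more than one direct line manager and not all of them take part, a situation the article neither states nor excludes. In that situation the participant rule places employees trained at T2 inside delayed departments during their control period, and the department rule counts employees of untrained supervisors as NC + NN.

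The size cannot be determined from the article. The 10% to 30% shares and the 0.80 effect show how the loss would scale; they are not estimates, and nothing in the text shows that the share exceeds zero. It would go too far to conclude that randomization is broken. The supportable conclusion is that two sections must be reconciled before departments are allocated. Severity is moderate.

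**What to change.** Align section 2.5 with section 2.1 through one department-level rule:

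- Before randomization, record which direct line managers of enrolled employees have agreed to NN, and classify each department once.
- State the manager-participation criterion. Requiring all of these managers to agree leaves no untrained supervisors in Groups 1 and 3 at allocation. A looser criterion accepts some dilution, which should then be acknowledged.
- Randomize only departments that meet the criterion, and place every other department whole in Group 2.
- Reassign no participant or department afterwards, and analyse everyone in the group first allocated.
- State that volunteering managers in Group 2 departments do not receive NN during the study period. Otherwise mixed departments would bring NN into the arm meant to be NC only and blur the comparison of Group 1 with Group 2.

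The cost is rewording of sections 2.1 and 2.5 and one question before randomization. The downsides are somewhat fewer randomized departments, more so if mixed departments prove common, and NN withheld from or deferred for some willing managers.
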